**Professionals**										
Job satisfaction			✓		Job satisfaction, subscale from the Consultants' Mental Health Questionnaire	✓				✓
Gender				✓	SCPD questionnaire	✓				

**Informal caregivers**										
Sense of competence		✓			SCQ	✓				✓
Quality of life		✓			EQ-5D	✓				✓
Depressive symptoms		✓			CES-D	✓				✓
Caregiver distress		✓			NPI-Q	✓				✓
Time spent giving care			✓		RUD	✓	✓	✓	✓	✓
Age				✓	RUD	✓				
Gender				✓	RUD	✓				
Ethnicity				✓	RUD	✓				
Education				✓	RUD	✓				
Marital status				✓	RUD	✓				✓
Living arrangement				✓	RUD	✓				✓
Relation with the patient				✓	SCPD questionnaire	✓				
Shared household with the patient				✓	SCPD questionnaire	✓				✓

**People with dementia**										
Housing conditions/residence	✓		✓	✓	RUD	✓	✓	✓	✓	✓
Quality of life		✓			Qol-AD	✓				✓
Behavior problems		✓			NPI-Q	✓				✓
Healthcare services used			✓		RUD	✓	✓	✓	✓	✓
Severity of dementia				✓	DSM-III-TR	✓				
Age				✓	RUD	✓				
Gender				✓	RUD	✓				
Ethnicity				✓	RUD	✓				
Education				✓	RUD	✓				
Marital status				✓	RUD	✓				✓
Living arrangement				✓	RUD	✓				✓
Children				✓	RUD	✓				
Children living in				✓	RUD	✓				

PO, primary outcome; SO, secondary outcome; EE, economic evaluation; BG, background; T0, baseline measure; T1, 3-month follow-up measure; T2, 6-month follow-up measure; T3, 9-month follow-up measure; T4, 12-month follow-up measure; CES-D, Center for Epidemiologic Studies Depression Scale; DSM-III-TR, Diagnostic and statistical manual of mental disorders, 3^rd ^text revision; EQ-5D, EuroQol-5D; NPI-Q, Neuropsychiatric Problems Inventory Questionnaire; Qol-AD, Quality of Life in Alzheimer's Disease; RUD, Resource Utilization in Dementia; SCQ, Sense of Competence Questionnaire; SPCD, Systematic Care Program for Dementia.

### Outcome parameters

Table 1 presents the types of data used for the outcome parameters:

1. The primary outcome measure is the institutionalizing of the person with dementia in a nursing home during the 12-month follow-up period. Both the institutionalization rate and the time to institutionalization will be taken into account. Possible institutionalization will be assessed every 3 months with one item of the Resource Utilization in Dementia questionnaire[42].

2. The secondary outcome measure is the quality of the caregiver's and the patient's lives. The quality of the caregiver's life will be measured with the Sense of Competence Questionnaire [35], the EuroQol-5D [43,44], the Center for Epidemiologic Studies Depression Scale [45,46], and the caregiver distress will be assessed with the Neuropsychiatric Inventory Questionnaire [47,48]. The patient's quality of life will be measured with the Neuropsychiatric Problems Inventory Questionnaire and the Quality of Life in Alzheimer's Disease [49,50].

Baseline variables as well as sociodemographic characteristics of both the patient and the informal caregiver are control variables. Sociodemographic characteristics are the severity of the patient's dementia according the DSM-III-TR [41], and the caregiver's relation to the patient and their living arrangements. The health service, gender, and job satisfaction [51,52] of the professional are also control variables.

Concerning the effect of the intervention on emotional functioning we expect positive changes on the secondary outcome quality of life – e.g. depressive symptoms, patients' problem behavior and caregiver distress as related to patients' problem behavior, sense of competence, and both caregiver and patient quality of life – at 12 months follow-up, in favor of caregivers and patients involved in the intervention group, as compared to controls.

### Process evaluation

A process analysis of the intervention will be carried out to gain insight into factors that might influence success or failure of the intervention [53,54]. This process analysis is a description of the actual exposure of both the professional and the caregiver to the SCPD as planned and the experience of the professionals with the SCPD. For this purpose, the following questions will be examined retrospectively:

1. Were professionals trained in the SCPD as planned?

2. Did the informal caregivers receive the care as planned?

3. What is the relationship between the results when the SCPD was carried out as planned and the outcome measures of institutionalization, time to institutionalization, and the quality of the caregivers' lives?

4. What are the professionals' obstacles and facilitators for carrying out the SCPD as planned?

A triangulation of methods and data collection will be used to guarantee the internal validation of the process evaluation [55,56]. First, content analysis [57,58] will be used to determine whether the intervention group have been trained as planned. For this purpose, the data collected during the study period about the participation of professionals in one or more parts of the training sessions will be scored. Second, content analysis of the starter packages and action lists returned to us will be used to determine whether the caregivers received care from the intervention group as planned. The 11 items of the SCPD screening tool must have a score of 100% before we can assume that the caregiver has received care from the professional as planned. Because it is not possible to directly deduce whether the care received differs from the care planned, at least two items on the action list should be scored to make is credible that the caregiver received the care planned. We will present the results of both content analyses in tables of frequencies with cross tabulation.

These results will be the main input for the third question of the process evaluation, "What is the relationship between the results when the SCPD was carried out as planned and the outcome measures of institutionalization, time to institutionalization, and the quality of the caregivers' lives?" In answering this question, the carrying out of the SCPD as planned will be summarized as the product of two scores, namely, the score with professionals trained as planned and the score with caregivers receiving the care as planned. Next, this score will be used as the input for multilevel logistic and multilevel linear regression analyses for the relationship of the carrying out of the SCPD as planned to the institutionalization, time to institutionalization, and the quality of the caregivers' lives. The gender of the professional will be treated as a control variable to adjust for the characteristics of the professional. All process evaluation analyses will be done with SPSS version 16.0 (SPSS, Chicago, Illinois) and MLwiN Version 2.0 (Centre for Multilevel Modelling, University of Bristol, Bristol, UK).

Semi-structured interviews will be used to explore professionals' obstacles and facilitators in carrying out the SCPD as planned. Three key informants allocated to the intervention group from each health service will be interviewed. Purposive sampling [59] will be used to select a varied group of professionals from each health service on the basis of scores pertaining to professionals who carried out the SCPD as planned. In this approach, seven levels for exploring obstacles and facilitators are recognized: the intervention itself, the innovation itself, the individual professional, the patient (e.g., the caregiver), the social context, the organizational context, and the economic and political context [60]. The records of the evaluation sessions with professionals as part of their SCPD training, as well as information collected from two pilot interviews with professionals, will be used as input for developing question sets at each level. The interviews will be audio-taped and transcribed. Two investigators will use the modified grounded theory approach to analyze them independently [61-63]. We assume that 18 interviews will be enough to reach the point of theoretical saturation. If not, the purposive sampling procedure will be repeated, and additional interviews will take place until no new information about the obstacles and facilitators appear. The software package SPSS version 16.0 will be used for the purposive sampling procedure, and Atlas.ti 5.2 will be used for the qualitative analysis.

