**Figure 2 F2:**
[figure not shown]
**Screening tool for the Systematic Care Program for Dementia**.

2. *Psychosocial support*. The SCPD is flexible in connecting pro-active interventions to individual problems. Professionals use strategies aimed to support caregivers; for example, instructions on how to deal with the patient's behavioral problems. The clarification of the relation between the disease and the patient's problematic behavior is a SCPD support strategy. One goal might be that the caregiver will not take difficult behavior personally, which can diminish mutual negative feelings considerably. Professionals provide data about their support and interventions (actions) during and after each contact with the patient-caregiver dyad.

3. *Transfer to regular healthcare*. Along with psychosocial support, professionals might negotiate or organize respite care, which is like home care or day care. If the screening for caregiver depression gives cause for further screening for clinical depression, the professional may also refer the caregiver or start treatment. Professionals provide data about the organization and management of care if the case is transferred to other institutions or professionals.

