The cost analysis will consist of two main parts. In the first part, on the patient-caregiver dyad level, we will measure volumes of care prospectively, using the RUD questionnaire [42,64]. This instrument contains questions about the use of community care services, type of accommodation, the employment status of the person with a cognitive disorder and the primary informal caregiver, medical care, and informal care. Informal care-giving time will be categorized as a loss of production (friction-cost method) for an employed primary caregiver, and as a loss of leisure time in all other cases. The RUD instrument will be completed by the informal caregiver every 3 months from baseline to follow-up at 12 months. The time to institutionalization is the final event. In both treatment groups, SCPD and usual care, the patients who are still not institutionalized at the end of 12 months are considered as censored observations. The second part of the cost analysis consists of determining the cost prices for each volume of consumption in order to be able to multiply the volumes registered for each participating caregiver and each patient. The Dutch guidelines for cost analyses will be used [65]. If no guideline or standard prices are available for units of care/resources, we will determine real cost prices with the activity-based costing method [66,67].

The effect analysis will adhere to the design of a cluster, randomized, controlled trial. The relevant variables for the economic evaluation are the time to institutionalization and the quality of the caregiver's life. We will use QALYs computed with the trapezium rule for a cost-utility analysis of the two treatment groups. The time to institutionalization will be the final event, meaning that the quality of the caregiver's life will be researched until the time of the patient's institutionalization, with a maximum of 12 months. We will use the standard EQ-5D [43,44] classification system developed by the EuroQol Group for the overall quantification of health status as a single index (utilities). The EQ-5D is one of three widely used multi-attribute systems available to determine health state preferences (utilities). The arguments for choosing the EQ-5D are:

1. The five domains of the EQ-5D reflect aspects that are thought to be important for the population under consideration.

2. The system is relatively simple to administer.

3. The sensitivity of the instrument has proven satisfactory.

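### The process evaluation assigns time to institutionalization to logistic and linear models that make no provision for censoring, and scores fidelity over follow-up with no fixed window

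*Protocol article*

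**What the plan says.** Question 3 of the Process evaluation section asks how delivery of the programme as planned relates to outcome. Fidelity is "summarized as the product of two scores, namely, the score with professionals trained as planned and the score with caregivers receiving the care as planned". Care counts as received when all 11 screening items are scored and, in addition, "at least two items on the action list should be scored". Under the psychosocial-support stage of the intervention description, "Professionals provide data about their support and interventions (actions) during and after each contact with the patient-caregiver dyad". No cut-off date is given for counting actions.

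For the analysis, "this score will be used as the input for multilevel logistic and multilevel linear regression analyses", relating fidelity "to the institutionalization, time to institutionalization, and the quality of the caregivers' lives". On covariates the section adds: "The gender of the professional will be treated as a control variable to adjust for the characteristics of the professional".

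Two other sections treat the same outcome as a survival time. In the Economic evaluation, "the patients who are still not institutionalized at the end of 12 months are considered as censored observations". The Statistical analyses section names Kaplan-Meier and a Cox model for it.

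**The concern.** Time to admission is a censored outcome. As worded, the process evaluation offers only two model types, and neither accommodates censoring unless it is set up specially. A linear model forces a choice: enter 12 months as if it were the admission time, or drop everyone not admitted. Dyads that drop out or in which the patient dies before 12 months have no usable time under either choice.

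The second issue is timing. The care-received component is built from records made during follow-up. A patient admitted in month 1 has had less opportunity to reach two recorded actions than one still at home in month 12. Low fidelity can therefore be partly a consequence of early admission.

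At stake is the answer to question 3, which is meant to help explain why the programme succeeds or fails.

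**Working it through.** **1. The planning rate and the censored share.** The Power calculations section gives 14% against 28%, two-sided 0.05, 80% power, 132 per group. With pooled variance:

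n = [1.960·√(2·0.21·0.79) + 0.8416·√(0.14·0.86 + 0.28·0.72)]² / 0.14² = (1.129 + 0.478)² / 0.0196 ≈ 131.7, so 132. Then 132 × 1.15 = 151.8, so 152. Both figures reproduce.

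Censored share in the intervention arm = 1 − 0.14 = 86%. Of 152 dyads: 152 × 0.14 ≈ 21 events and 131 without an event. Taking instead 190 enrolled less 25% dropout: 142.5 × 0.14 ≈ 20 events and about 122 without. If the control rate of 28% applied, the censored share would be 72%.

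**2. What a linear model does with these times.** Assume exponential times with 14% admitted by 12 months in the reference group, and a fidelity effect that halves the hazard (both assumptions).

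- Capped mean: (1 − e^(−12λ)) / λ.
- Mean in admitted cases: [capped mean − 12·e^(−12λ)] / (1 − e^(−12λ)).

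| | λ per month | Admitted by 12 months | Capped mean | Mean, admitted only |
|---|---|---|---|---|
| Reference | −ln(0.86)/12 = 0.01257 | 0.140 | 11.14 | 5.85 |
| Full fidelity | 0.00628 | 0.073 | 11.56 | 5.92 |
| Difference | | | 0.42 months | 0.08 months |

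Simulation of the same set-up gave 0.42 and 0.07 months, with 89% censored when half the dyads have full fidelity. With a hazard ratio of 1 and fidelity fixed at baseline, the capped difference was 0.00 months. Restricting to admitted cases therefore nearly erases a real relation. Capping keeps a small signal and creates no false one, provided nobody is lost before 12 months.

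**3. Timing of the score.** Assume no true effect, a 14% admission rate, a yes/no score that a share p of dyads would eventually meet, and an exponential time to meeting it with mean w (so μ = 1/w). For p = 0.9 and w = 1 month:

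- Admitted, score met: 0.9 × [0.14 − 0.01257/(0.01257 + 1)] = 0.1148.
- Not admitted, score met: 0.9 × 0.86 = 0.7740.
- Admitted, not met: 0.14 − 0.1148 = 0.0252.
- Not admitted, not met: 0.86 − 0.7740 = 0.0860.
- Odds ratio: (0.1148 × 0.0860) / (0.7740 × 0.0252) ≈ 0.51.

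Simulation with 152 dyads, clustering ignored, p from 0.6 to 0.9:

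| Mean time to meet the criterion | Odds ratio, no true effect | False protective finding |
|---|---|---|
| First contact | 1.00 | 1% |
| 1 week | 0.95 to 0.80 | 2 to 3% |
| 1 month | 0.81 to 0.51 | 9 to 11% |
| 3 months | 0.56 to 0.27 | 37 to 62% |

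The form of the score matters too. With 5 actions at the start and 0.5 more per month (assumed), a raw count correlates 0.36 with time at home and gives a false finding 99% of the time. The two-action threshold on the same counts correlates 0.11 and gives 27%. If six extra crisis actions precede admission, the correlation of the count turns negative (−0.15). The documents give no completion times or action rates, so none of these rows can be singled out.

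**The case against.** The strongest reply is that the criterion is modest and can be met early. The programme can begin at the first consultation, screening is its first stage, and the 60-item action list includes intake, diagnostics and psychoeducation. The training factor belongs to the professional and does not grow with a dyad's time at home. If two actions are recorded at the first visit, the timing bias vanishes. This stands. A reader might infer that faithful delivery will look protective by construction; the documents do not support that, because the bias may be nil, large or reversed.

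Nor does censoring supply that inference. With complete follow-up to 12 months, the capped time is fully observed and gives no spurious difference. This also stands, but the plan itself expects 25% dropout and stops follow-up at death.

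A multilevel logistic model fitted to the 3-monthly assessments could serve as a discrete-time hazard model. The wording does not exclude this, but it does not say so either, and a linear model is named beside it.

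A reader might also take the professional's gender to be the only adjustment. That over-reads the text. The sentence concerns characteristics of the professional, and the Outcome parameters section separately declares baseline variables, dementia severity and living arrangements to be control variables. Likewise, a reader might extend the point to the per-protocol analysis, but that set is not defined in the article and nothing ties it to this score.

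Finally, an article may leave a fidelity window to the full plan. That carries some weight for the window. It carries less for the models, which the article does name and which do not match its own treatment of the outcome.

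**Conclusion.** The point holds in limited form. The models named for question 3 conflict with the article's own handling of time to institutionalization, and a linear analysis would be invalid for dyads lost before 12 months. It would also be nearly uninformative if confined to the roughly 20 admitted cases. The 86% is a planning figure from previous research, not an observed rate, and the 0.42 and 0.08 month figures rest on exponential times and an assumed halving of the hazard.

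The absence of a fidelity window leaves room for early admission to lower the score. How much, and in which direction, cannot be settled from the documents. That uncertainty is a reason to fix the timing before analysis; it does not show that the result will be biased. The analysis is secondary and observational. The primary intention-to-treat comparison is untouched, and no claim is made about the per-protocol set.

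**What to change.** For question 3, reword the Process evaluation section as follows:

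- Analyse time to institutionalization with a discrete-time multilevel hazard model on the 3-monthly assessments, or a Cox model with a professional-level frailty, with censoring at 12 months and at earlier loss. Keep the logistic model for admission yes/no and the linear model for quality of life.
- Define fidelity within a fixed early window, for example up to T1 (3 months), and start follow-up for this analysis at that landmark among dyads still at home. Alternatively, enter fidelity as a time-dependent covariate.
- State that the control variables in the Outcome parameters section (dementia severity, living arrangements, baseline sense of competence) also apply here, as far as the number of events allows.

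The cost is wording only, since the action lists and baseline measures are already collected. The downside is lost events. With a constant hazard, 1 − 0.86^(3/12) ≈ 3.7% of dyads are admitted before T1, or 152 × 0.037 ≈ 6 of about 21 events. About 15 remain, which supports very few covariates. The time-dependent version keeps the early events but needs dated action records.

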**Figure 3 F3:**
[figure not shown]
**Training program for the Systematic Care Program for Dementia**.

1. *The SCPD screening tool*. The questions for the screening a caregiver's sense of competence and depressive symptoms are printed on a handy plasticized pocket card.

2. *The SCPD manual*. The manual consists of the items to be discussed during the training sessions (i.e., background information and methods), and some supporting literature has been added.

3. *The starter package and action list*. Several forms have been developed for the requested data. The starter package contains the forms that professionals need to gather these data. The action list contains 60 possible intervening and supportive actions that professionals might undertake as a result of the screening. They are divided into nine categories: intake, diagnostics, psychoeducation, psychosocial care, medical care, how to hand over care, legal care, case management, and crisis management. The list was developed in collaboration with a staff member and a social psychiatrist from each of the original three participating health services. Each person involved listed potential intervention and support actions. Repeatedly mentioned actions were included in the action list. Consensus for including actions on this list was reached.

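### The process-evaluation models name only the professional's gender as a control variable, which leaves the non-randomized fidelity coefficient open to confounding by the dyad's baseline need

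*Protocol article*

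**What the plan says.** The Process evaluation section of the protocol article sets out the exposure, the models, the outcomes and one covariate.

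- Exposure: "the carrying out of the SCPD as planned will be summarized as the product of two scores", one for the professional's training and one for the care the caregiver received. Care counts as delivered when all 11 screening items are complete and "at least two items on the action list should be scored".
- Models: "this score will be used as the input for multilevel logistic and multilevel linear regression analyses", with institutionalization, time to institutionalization and caregiver quality of life as outcomes.
- Covariate: "The gender of the professional will be treated as a control variable to adjust for the characteristics of the professional".

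Two other places bear on this. The description of the action list, under Training in the Systematic Care Program for Dementia, speaks of "supportive actions that professionals might undertake as a result of the screening". The Outcome parameters section states for the study in general that "Baseline variables as well as sociodemographic characteristics of both the patient and the informal caregiver are control variables", and adds the health service and the professional's gender and job satisfaction. The Statistical analyses section applies the control variables by name only in the Cox model for time to institutionalization. Table 1 shows that the SCQ, EQ-5D, CES-D, NPI-Q and dementia severity are all recorded at T0.

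**The concern.** Randomization protects the comparison of the two arms. It does not protect a comparison of dyads who received the programme as planned with dyads who did not. The screening that prompts actions covers the caregiver's sense of competence and depressive symptoms, and the SCQ and CES-D measure the same constructs as outcomes at 12 months. A caregiver who starts in a worse state may prompt more recorded actions and also be expected to finish in a worse state. The likeliest confounder is therefore close to the T0 value of the outcome itself, and adjusting for the professional's gender cannot remove it.

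This analysis is meant to explain why the programme succeeded or failed. If the models are run with the named covariate alone, delivery as planned could appear to go with worse quality of life or more admissions merely because needier dyads received more actions. If instead the most burdened dyads received less complete care, delivery could look beneficial for an equally spurious reason. Either result would colour the reading of the main trial finding.

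**Working it through.** The article gives no sample size, power or correlation for these models, so there is no planned figure to reproduce for them. The correlations below are assumptions, shown over a range. From Power calculations come the 14% institutionalization rate in the intervention group and the 152 dyads per group before dropout inflation (132 × 1.15 = 151.8).

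**Linear quality-of-life outcomes.** Let g be the correlation of baseline need with fidelity and r the correlation of baseline need with the 12-month outcome. All variables are standardized, and the true fidelity effect is zero.

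- Spurious coefficient without baseline adjustment = g × r.
- Standard error, adjusted over unadjusted = √[(1 − r²) / ((1 − g²r²)(1 − g²))].

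Each cell gives the spurious coefficient, in SD of outcome per SD of fidelity, with the standard-error ratio in brackets.

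| g | r = 0.3 | r = 0.5 | r = 0.7 |
|---|---|---|---|
| 0 | 0 (0.95) | 0 (0.87) | 0 (0.71) |
| 0.1 | 0.03 (0.96) | 0.05 (0.87) | 0.07 (0.72) |
| 0.2 | 0.06 (0.98) | 0.10 (0.89) | 0.14 (0.74) |
| 0.3 | 0.09 (1.00) | 0.15 (0.92) | 0.21 (0.77) |

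For example, at g = 0.3 and r = 0.5 the shift is 0.3 × 0.5 = 0.15. A negative g gives the same sizes with the sign reversed. Adjustment also sharpens the estimate in most cells, but not when both correlations are 0.3.

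**Institutionalization.** A simulation used 152 dyads, about half of them delivered as planned, roughly 12 to 15% events, no clustering and a true odds ratio of 1. There were 600 replicates per row; those with an unadjusted log odds ratio beyond ±5 or a failed fit were dropped. Need effects are log odds ratios per SD.

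| Need on fidelity | Need on institutionalization | Unadjusted OR | Adjusted OR | SE of log OR, unadjusted | SE of log OR, adjusted |
|---|---|---|---|---|---|
| 0 | 0.5 | 0.99 | 0.99 | 0.515 | 0.527 |
| 0 | 1.0 | 1.00 | 1.00 | 0.494 | 0.529 |
| 0.5 | 0.5 | 1.31 | 1.04 | 0.515 | 0.541 |
| 0.5 | 1.0 | 1.54 | 0.99 | 0.497 | 0.542 |
| 1.0 | 0.5 | 1.54 | 1.00 | 0.519 | 0.578 |
| 1.0 | 1.0 | 2.17 | 0.99 | 0.515 | 0.586 |

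Adjustment removes the bias from the measured confounder, but the standard error rises slightly. Time to institutionalization was not simulated; it rests on the same events.

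**How many covariates the event count supports.** Expected events in the intervention group, where fidelity is assessed: 0.14 × 152 = 21.3, about 21.

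- Long list: fidelity, professional's gender, severity, NPI-Q, SCQ, CES-D and shared household (7 parameters) plus six services as fixed effects (5 more) make 12. That gives 21 / 12 = 1.75 events per parameter.
- Short list: fidelity, professional's gender and one baseline covariate make 3, or 21 / 3 = 7 events per parameter. With two baseline covariates it is 21 / 4 = 5.25.

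**The case against.** The strongest reply is that the quoted sentence limits its own scope. It names gender to deal with the professional's characteristics and does not exclude dyad-level covariates. The general statement under Outcome parameters could be read as covering these models too, and a journal article may leave the full covariate list of a secondary model to the full plan. This stands in part. A reader might infer that adjustment is for gender and nothing else, but the article does not say so. It does, however, write down a covariate choice for these particular models, narrower than its own general list. That makes it a point to reconcile rather than a permissible silence.

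A second reply is that fidelity may depend little on need. One factor of the score is training attendance, which belongs to the professional. Completing all 11 items looks like the professional's diligence. Two actions out of 60 is a low bar, since the categories include intake and diagnostics. The direction may also reverse: a dyad whose patient is admitted early has fewer contacts in which actions can be recorded, which would tie low fidelity to worse outcomes. All of this stands. It rules out stating confounding as a fact or fixing its sign. The reversal through early admission would not be cured by baseline adjustment either.

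A third reply is that precision is not generally lost. That is right for institutionalization, as the simulation shows. A reader might also infer a power gain for the fidelity effect, but the article's 80% power belongs to the randomized comparison and none is stated here.

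**Conclusion.** The point holds as a minor one. A non-randomized score is related to outcomes with one named covariate that cannot address baseline need, while suitable baseline values are collected and are called control variables elsewhere in the article. The fidelity coefficient is open to confounding. Under the assumed correlations the size is about 0.03 to 0.21 SD per SD of fidelity for linear outcomes, and a spurious odds ratio of about 1.3 to 2.2 for institutionalization. It is nil if fidelity is unrelated to need.

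The documents do not support three stronger readings: that the coefficient is certainly biased, that it is biased against the programme, or that every model loses precision. Size and direction depend on correlations the article does not give, and the precision gain is confined to the linear outcomes, in most settings. Nor is the trial's main result in question, because the randomized comparison does not use this score.

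**What to change.** In the Process evaluation section:

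- For each linear quality-of-life model, add the T0 value of the same scale and keep the professional's gender.
- For institutionalization and time to institutionalization, add at most one or two baseline covariates, for example dementia severity, or a single baseline risk score. The reason is to reduce bias, not to gain precision.
- State which of the control variables under Outcome parameters apply to these models, so that the two sections agree.
- Report the results as adjusted associations, since only measured confounding is removed.

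The cost is a change of wording and a few extra model parameters. The variables named are already collected at T0.
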